## Abstract

**Background:**

Cardiac rehabilitation has a beneficial effect on the prognosis and quality of life of cardiac patients, and has been found to be cost-effective. This report describes a comprehensive and low cost educational intervention designed to increase the attendance at cardiac rehabilitation programs of patients who have undergone coronary artery bypass graft surgery.

**Methods/Design:**

A controlled prospective intervention trial. The control arm comprised 520 patients who underwent coronary artery bypass graft surgery between January 2004 and May 2005 in five medical centers across Israel. This group received no additional treatment beyond usual care. The intervention arm comprised 504 patients recruited from the same cardiothoracic departments between June 2005 and November 2006. This group received oral and written explanations about the advantages of participating in cardiac rehabilitation programs and a telephone call two weeks after hospital discharge intended to further encourage their enrollment. The medical staff attended a one-hour seminar on cardiac rehabilitation. In addition, it was recommended that referral to cardiac rehabilitation be added to the letter of discharge from the hospital. Both study groups were interviewed before surgery and one-year post surgery. A one-year post-operative interview assessed factors affecting patient attendance at cardiac rehabilitation programs, as well as the structure and content of the cardiac rehabilitation programs attended. Anthropometric parameters were measured at pre- and post-operative interviews;- and medical information was obtained from patient medical records. The effect of cardiac rehabilitation on one- and three-year mortality was assessed.

**Discussion:**

We report a low cost yet comprehensive intervention designed to increase cardiac rehabilitation participation by raising both patient and medical staff awareness to the potential benefits of cardiac rehabilitation.

**Trial registration:**

ClinicalTrials.gov: NCT00356863

## Background

When we initiated this interventional study in 2004, the effectiveness of cardiac rehabilitation (CR) programs for promoting health, psychological status and functioning; and for decreasing symptoms of angina pectoris and heart failure, in post-coronary artery bypass graft (CABG) patients had already been well established [1-5]. Though shown to be highly cost effective [6,7], CR programs reported low participation rates [8]. Low referral rates and low patient motivation, both of which were due to lack of knowledge regarding potential health benefits, were identified as the main barriers to cardiac rehabilitation [9,10]. Simple interventions, such as two post-CABG telephone calls [11] and more comprehensive CR programs [12] demonstrated positive effect.

We designed a simple intervention aimed to increase participation of post-CABG surgery patients in CR programs, by increasing patient and staff awareness of the benefits, availability, and patient eligibility to participate in these programs.

## Methods/Design

### Study initiation

#### Aim

The overall aim was to assess the effect of an easy-to-implement intervention on participation of post-CABG patients in CR programs.

#### Specific Objectives

1. To examine the effect of a hospital-based intervention program on the rate of attendance of post-CABG patients at CR programs;

2. To investigate the effect of sociodemographic factors on CR participation;

3. To assess the effect of CR participation on medical as well as psychological outcomes of post-CABG patients, and on their quality of life.

#### Hypotheses

1. We hypothesized that raising the awareness of the potential health benefits of CR among medical staff and CABG patients would significantly increase patient attendance at CR programs;

2. We hypothesized that patients who participated in CR would show greater improvements in medical outcomes and quality of life, reduced levels of anxiety and depression, and increased 1 and 3-year survival rates, compared to patients who did not participate in CR.

#### Design

A controlled prospective study (Figure 1). The control arm comprised 520 patients who underwent CABG surgery between January 2004 and May 2005 in five medical centers across Israel. The intervention arm comprised 504 patients recruited from the same cardiothoracic departments between June 2005 and November 2006. Since the intervention included a seminar for the cardiothoracic unit staff, all patients in the control arm were recruited first. To avoid contamination, the implementation of our intervention and recruitment of the intervention arm took place upon completion of the control phase. In both arms, we approached consecutive patients scheduled for CABG surgery. Consenting patients were interviewed before surgery and one-year post surgery. The intervention group received oral and written explanation about CR programs and a telephone call after hospital discharge. In addition, the medical staff attended a one-hour seminar on CR and it was recommended that referral to CR be added to the patient letter of discharge. The control group received no additional treatment beyond usual care.

**Figure 1 F1:**
[figure not shown]
**Study Design**.

#### Selection of participating cardiothoracic units

We approached cardiothoracic units within medical centers located in different geographical regions of Israel, and of different affiliations (private, governmental, and health maintenance organization). The goal was to obtain a representative sample of the CABG patient population in Israel, regarding socioeconomic and ethnic characteristics, and health maintenance organization affiliation. We achieved collaboration with five medical centers. Agreement was initially sought from the medical director of each center, and subsequently from the head of each cardiothoracic ward and its head nurse. No directed action to increase cardiac rehabilitation rates had been taken in the participating cardiothoracic units prior to the study.

#### Calculation of sample size and study duration

We calculated sample size to enable detection of significant differences between patients in the intervention and control arms in the rate of participation in CR. We used estimates for these rates from published data on self-reported participation in CR in post-CABG patients [8]. The calculations for power, comparing the proportions [13] of participation in rehabilitation in the two arms, using a two-sided test with significance alpha = 0.05 and size of groups n1 = n2 = 430, and assuming that the proportional CR participation rate at baseline is 7%, yielded 90% power to detect a difference of 7% following intervention (that is, a rehabilitation rate of 14% in the intervention group). We assumed that up to 15% of the sample would fail to complete all the study items. Therefore, we increased the sample size accordingly to compensate for missing values. Thus, the targeted total for the intervention and control arms were 500 patients each, or 1000 in total.

According to data provided by the Israeli Ministry of Health, a total of 1596 CABG operations were carried out in the five units participating in the study during the year 2003. Assuming that these figures remained stable, and that exclusion criteria and refusal rate would reduce potential participation by 40%, we expected to reach our target sample of 1000 CABG patients (including pilot sample) within 15 months from study initiation. In reality, study was initiated in the five units at different times, as after the Institutional Review Board (IRB) approvals were obtained. As a result, the total duration of patient recruitment was longer than initially anticipated. The first 520 patients who enrolled in the study (from January 2004 to May 2005) composed the control arm. The following 504 patients, recruited between June 2005 and November 2006, composed the intervention arm (Figure 1).

We excluded from the study patients with severe co-morbidities for whom CR is contra-indicated (e.g. CHF stage IV); patients who were unsuitable for interview prior to their operation, i.e. patients undergoing emergency CABG operation; institutionalized patients; and patients with severe cognitive impairment (e.g. general stroke with severe disability); patients who did not understand any of the languages in which the study was conducted: Hebrew, English, Russian, and Arabic; and patients residing farther than 30 km from a rehabilitation center, due to the difficulty for these patients to commute to a CR facility.

For standardization, we interviewed all patients during their pre-surgery hospitalization. Patients who could not be interviewed prior to surgery (e.g. due to emergency operation) were not included since their mental or cognitive state could be affected by general anesthesia and CABG surgery (Figure 2).

**Figure 2 F2:**
[figure not shown]
**Study population and study sample**.

### Procedure

#### Pilot study

We examined the pre-operative and post-operative questionnaires of the first 12 patients scheduled for CABG surgery in the cardiothoracic unit of the Hadassah Medical Center, Jerusalem, the first medical center in which we obtained IRB approval. We amended the interview protocol according to the results and feedback from this pilot study.

#### Study initiation, and recruitment of the control arm

Prior to recruitment, we presented the technical and logistic aspects of the study to the staff at each participating cardiothoracic unit. We recruited participants for the control arm from consecutive patients who were hospitalized while waiting for CABG surgery. Assisted by the chief nurse at each unit, a trained interviewer assessed each candidate's eligibility for participating in the study. After obtaining written informed consent, personal interviews were carried out, anthropometric measures obtained, and medical information e.g. results from blood tests, extracted from patients' medical chart.

#### One year follow up interview

Participants were approached again for a second interview one year after CABG surgery. Interviews were carried out by trained interviewers at participants' homes. The assessment included an interview and obtaining anthropometric measures and medical information from medical documents. Assessment at both time-points took approximately 60 minutes to complete. Patients were asked to prepare medical documentation for the interview. Those refusing a home interview were contacted by telephone; they provided information only regarding their attendance in a CR program (n = 118).

#### Intervention

We first asked physicians and nurses in each participating cardiothoracic unit to complete a short questionnaire to assess their level of knowledge regarding the content and provision of CR programs within the Israeli national healthcare system. This was followed by a one-hour seminar that included information for medical staff on the potential benefits of cardiac rehabilitation for patients and the provision of these programs within the healthcare system in Israel.

Recruitment and interviewing of the intervention arm was identical to that described for the control arm. In addition, patients in the intervention arm participated in an educational program that included 4 elements:

1. An individual 10-minute consulting session conducted during the hospital stay, prior to CABG surgery. We explained the benefits of cardiac rehabilitation, the content of such programs, criteria for patient eligibility for CR under the Israeli National Health Insurance Law, and the contact details of CR programs available in Israel and of the health maintenance organization (HMO) to which patients were affiliated. Sessions were delivered in Hebrew, English, Russian, and Arabic.

2. Pamphlets specially prepared for this study, in Hebrew and Russian, were distributed to patients at the end of the consultation session. The content was the same as that presented orally.

3. The director of each participating cardiothoracic ward was asked to issue each patient an explicit recommendation for participation in a CR program in their letter of discharge.

4. Two to three weeks after discharge from the hospital, each patient received a telephone call from a trained interviewer inquiring whether he or she intended to participate in a CR program. Patients were reminded of the importance of CR, and further encouraged to participate.

#### Mortality follow-up

The study included mortality follow-up at one-year and three-year post surgery. The study file will be merged with the Central Population Registry-Israel.

#### Validation of patient interviews

To verify and complete information on medications and comorbidities, as well as the respondents' self report on medical parameters, each interview was supplemented by information from patients' medical records: medical files, and medical documentation.

### Investigated variables

#### Main outcome (dependent) variables

Comparing intervention versus control groups: cardiac rehabilitation participation, assessed 1-year post surgery

Comparing participants and non-participants in cardiac rehabilitation: the following were recorded by a structured questionnaire administered twice, first at study entry (before surgery) and second at one-year follow up:

▪ Use of healthcare services during the previous 12 months, including the frequency of visits to a primary practitioner, the number of visits to a cardiologist, the number of re-admissions to the hospital or emergency department, and the reasons for these re-admissions.

▪ Lifestyle parameters associated with increased cardiovascular risk, including dietary habits, tobacco use, and employment status.

▪ Physical activity and change in exercise capacity; derived from a score on a standardized physical activity questionnaire. This questionnaire was validated against cardiorespiratory testing as a predictor of cardiovascular fitness [14].

▪ Mental health and quality of life, using the generic health-related quality of life SF-36 HRQL questionnaire [15,16].

▪ Quality of Life as assessed by the disease specific MacNew Heart Disease Health-related Quality of Life Questionnaire [17].

▪ Depression and Anxiety, measured using the Hospital Anxiety Depression Scale (HADS) questionnaire [18].

▪ Anthropometric and physiologic data: blood pressure (measured three times during the interview); BMI (calculated from weight and height measured during the interview), heart rate (measured during the interview), waist and hip circumference (measured during the interview); plasma glucose, hemoglobin, total cholesterol, HDL-cholesterol, LDL-cholesterol, triglycerides, WBC, ejection fraction (collected from medical records).

▪ All cause mortality (one-year and three-year follow-up) will be carried out by linking the study file with data from the Israeli Central Population Registry.

▪ For those who participated in a CR program: the type of program and its content, adherence to the program, co-payment and cost of service to the patient, satisfaction with the program, and barriers to adherence encountered by patients.

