#### Independent variables and potential confounding factors

▪ Social and demographic parameters: age, gender, marital status, number of years of education, occupation, employment status, self-reported level of income (categorized in relation to the national average household income).

▪ Barriers to the use of CR services: poor health, work or financial constraints, lack of means of transportation.

▪ Health maintenance organization (HMO) affiliation and insurance coverage. We note that four national medical insurers/providers operate in Israel and a number of other medical insurance companies provide complementary services.

▪ Previous cardiovascular morbidity defined from the following question: "Did you undergo any previous cardiac procedures or cardiac related hospitalizations?"

▪ Co-morbidity defined from the questions: "Do you suffer from any other disease and/or handicap? If so, please specify the disease(s)/handicap and age at first occurrence"; "Have you been hospitalized in the last 12 months? If so, please specify the cause and month of each hospital admission."

▪ Medical treatment information: medications prescribed. This information is complementary to the information on self-reported conditions associated with cardiovascular disease (i.e., hypertension, diabetes mellitus, and hyperlipidemia) and other chronic diseases. Data was supplemented by information from medical files at hospitals.

▪ Severity of coronary disease: % ejection fraction (available for about half the patients), number of occluded vessels prior to CABG.

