#### Methods for statistical analysis

The analysis will constitute two parts according to the main study hypotheses: the first analysis will compare the intervention and the control arms to assess the impact of the intervention on the rate of CR uptake, and to assess the role of mediating factors. The second analysis will compare participants in CR programs and patients who did not participate in CR programs to evaluate the impact of CR on medical and psychosocial outcomes.

Univariate associations between the outcome measures in the comparison groups, and by various independent covariates, will be explored using the χ^2^-test, t-tests, and non-parametric procedures. To test for differences between two populations regarding continuous variables, we will use the unpaired t-test for normally distributed variables and the Wilcoxon rank sum test otherwise. To test for differences between two groups for various outcomes, adjusting for risk factors and potential confounders, we will use the generalized linear model for continuous outcome variables and the logistic regression model for dichotomous variables.

The medical center where the operation took place will be examined as a confounder to account for differences in the populations treated at each cardiothoracic unit, in the medical approach implemented, and in possible effects on outcomes.

For investigation of the second goal, we will compare those who did and did not participate in a CR program using the same tests as for comparison of control and intervention groups. We are aware that participation or non participation in CR depends on other parameters and can not be considered as randomly assigned. Therefore, we will apply the propensity score approach. First we will build a model for the probability of participation in CR (i.e. the propensity score) that will be based on a set of demographic and medical variables. This propensity score will be used in the regression analysis of the effect of participation in CR on various outcomes.

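### For the comparison of CR participants with non-participants, re-admissions are counted from about the day of surgery, so an early re-admission that keeps a patient out of cardiac rehabilitation (CR) would be scored against non-participation

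*Protocol article*

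**What the plan says.** The second analysis compares patients who attended CR with those who did not. Its outcomes are listed in the protocol article under Main outcome (dependent) variables and come from a questionnaire "administered twice, first at study entry (before surgery) and second at one-year follow up". One item is "Use of healthcare services during the previous 12 months, including the frequency of visits to a primary practitioner", and the same item covers "the number of re-admissions to the hospital or emergency department, and the reasons for these re-admissions".

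On timing, One year follow up interview states: "Participants were approached again for a second interview one year after CABG surgery". CR participation is ascertained at that interview too, looking back over the same year.

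The only clue to when CR begins is in Intervention: "Two to three weeks after discharge from the hospital, each patient received a telephone call from a trained interviewer". The purpose of that call was to ask about intention to join CR and to encourage it.

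Under Methods for statistical analysis, "we will compare those who did and did not participate in a CR program using the same tests" as for the two arms. The section accepts that attendance was not random. It plans a propensity score built on demographic and medical variables, to be used in the outcome regressions. Independent variables and potential confounding factors lists poor health among the barriers to CR. It also gives a hospitalisation question: "If so, please specify the cause and month of each hospital admission".

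**The concern.** A 12-month recall taken one year after surgery reaches back to about the operation. CR participation is decided within that same year, and for most patients apparently not in its first weeks. An early re-admission can therefore come before the decision to attend and influence it. Such a patient is classified as a non-participant, and the re-admission is then counted as an outcome of not participating.

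This is reverse causation built into the outcome window, and it is not ordinary baseline confounding. A propensity score on baseline variables cannot see an event that happens after surgery. Adding the early admission to the score while still counting it in the outcome would put the same event on both sides of the model.

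At stake is part of hypothesis 2, that "patients who participated in CR would show greater improvements in medical outcomes and quality of life". Any error from this source would point the way the hypothesis predicts.

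**Working it through.** **The plan's own figure.** The only design calculation is the power for CR participation of 7% versus 14% with 430 per arm and two-sided alpha 0.05, stated as 90%. It reproduces: 91.9% without a continuity correction and 90.1% with one, and n = 430 with the correction. It concerns the arms, not re-admissions, and is not in dispute.

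**Order of events as documented**

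1. Outcome window: the 12 months before an interview held one year after surgery, so from about surgery.
2. Exposure: CR attended at any time in that year, ascertained at its end.
3. CR start: no date is given. Two to three weeks after discharge patients are still asked about intention, so most had presumably not started.
4. Control of selection: a propensity score on demographic and medical variables. No text sets a landmark, treats CR as time-dependent, or leaves out admissions before CR.

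**Illustration with no effect of CR.** Inputs:

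- p = 0.14, uptake in patients without an early re-admission. This is the planned intervention-arm rate, borrowed here.
- e = 0.05 to 0.20, risk of re-admission before CR could start (assumed).
- r = 0.5 or 0.25, the factor by which an early re-admission multiplies uptake (assumed).
- l = 0.20, later re-admission risk, the same in both groups (assumed).

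Formulas:

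- P(early | CR) = e·r·p / [e·r·p + (1−e)·p]
- P(early | no CR) = e·(1−r·p) / [e·(1−r·p) + (1−e)·(1−p)]
- P(any in 12 months) = 1 − (1 − P(early))·(1 − l)

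Case e = 0.10, r = 0.5:

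- P(early | CR) = 0.007 / (0.007 + 0.126) = 0.0526
- P(early | no CR) = 0.093 / (0.093 + 0.774) = 0.1073
- Any, CR: 1 − 0.9474 × 0.8 = 24.2%
- Any, no CR: 1 − 0.8927 × 0.8 = 28.6%
- Risk ratio 0.85, although CR does nothing

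| e | r | CR | no CR | RR |
|---|---|---|---|---|
| 0.05 | 0.5 | 22.1% | 24.3% | 0.91 |
| 0.10 | 0.5 | 24.2% | 28.6% | 0.85 |
| 0.15 | 0.5 | 26.5% | 32.8% | 0.81 |
| 0.20 | 0.25 | 24.7% | 37.5% | 0.66 |
| 0.10 | 0.75 | 26.2% | 28.3% | 0.92 |
| any | 1 | equal | equal | 1.00 |

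The last two rows show a milder influence on uptake, and none.

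**Other assumptions.** Fix overall uptake at 10.5% (the mean of 7% and 14%), early risk at 5-15%, later risk at 15% or 25%, and r between 0 and 0.5. The spurious risk ratio is then 0.51 to 0.93.

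**Check of the remedy.** Counting only later admissions gives a risk ratio of 1.00 in every scenario. That result relies on later risk being independent of early re-admission. Where it is not, the early admission becomes an ordinary confounder, which is why it belongs in the propensity model.

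**The case against.** The strongest reply is that the 12 months is a questionnaire recall period, not an analysis definition. The analysis section does not say how admissions will be windowed, and an article may leave that to an analysis plan. This stands only in part. The item appears under the heading for main dependent variables, for this very comparison. Followed as written, it counts admissions that precede CR, so the point concerns something stated and not something merely omitted.

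Second, the protocol acknowledges selection into CR and plans for it. It does, but the planned method addresses who attends, not when the outcome clock starts.

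Third, the size is uncertain, and this stands. Every re-admission input is assumed, and the start of CR is inferred from one telephone call. At most 906 patients gave a home interview (1024 − 118 telephone-only). At 10.5% uptake that is about 95 participants and 811 non-participants. The 4.4-point gap in the worked case compares with a standard error of √(0.242 × 0.758/95 + 0.286 × 0.714/811) ≈ 4.7 points, so it is roughly one standard error.

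Fourth, re-admission is one component of one item in a long outcome list, and hypothesis 2 does not name it. This also stands. A reader might take re-admission to be the study's main safety outcome, but the protocol article never describes it so.

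**Conclusion.** The point holds for the second analysis, conditionally. The re-admission and emergency-visit window opens before most patients could have begun CR, and the planned propensity score cannot take out events that lie inside the outcome. Bias in favour of CR follows if early re-admission reduces uptake. That is plausible, since the protocol itself lists poor health as a barrier, but the documents do not quantify it. Under the main assumptions the spurious risk ratio is about 0.91 to 0.66.

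A reader might infer that the plan favours CR whatever the facts. The documents do not support that: with no influence of early re-admission on uptake, the ratio is 1.00. Nor does the point reach the intervention versus control comparison or the sample size, because arm membership does not depend on events after surgery. Confidence is high in the mechanism and low in its size. The plan should be changed, because the analysis is still described as to come and the core change is cheap.

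**What to change.** In Main outcome (dependent) variables and Methods for statistical analysis, for the comparison of CR participants with non-participants only:

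1. Count hospital and emergency admissions only after a fixed landmark following surgery, chosen before the data are examined. Date them from the question on month of admission or from medical records. The question is listed under co-morbidity, so first confirm that it was also asked at the one-year interview.
2. Enter post-surgical admissions before the landmark as covariates in the propensity model.
3. Report the full 12-month count descriptively.
4. Where CR start dates can be recovered from existing data, classify participation by a start before the landmark, with a stated rule for later starters. The CR items listed for the interview include no start date, and the interviews appear to be complete, so a new item cannot be assumed. If start dates cannot be recovered, state as a limitation that some counted admissions may still precede CR.

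The cost is analysis wording and some checking of dates. Some events and precision are lost, including admissions during CR in patients who began before the landmark.

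### One-year survival by cardiac rehabilitation participation cannot be tested, because participation is learned only from patients alive at one year; the three-year comparison depends on an unstated rule for first-year deaths

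*Protocol article*

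**What the plan says.** Hypothesis 2 (Hypotheses) expects participants in CR to have "increased 1 and 3-year survival rates, compared to patients who did not participate in CR". Main outcome (dependent) variables puts mortality under the comparison of participants with non-participants: "All cause mortality (one-year and three-year follow-up) will be carried out by linking the study file". Mortality follow-up counts both horizons from surgery.

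The exposure is "cardiac rehabilitation participation, assessed 1-year post surgery". One year follow up interview gives the mechanism: "Participants were approached again for a second interview one year after CABG surgery", at home, with a telephone contact for 118 patients who refused the home visit.

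No other source of attendance is described:
- The call two to three weeks after discharge (Intervention) goes to the intervention arm only, "inquiring whether he or she intended to participate in a CR program". It records intention, not attendance.
- Record checks (Validation of patient interviews) are made "To verify and complete information on medications and comorbidities" and to check self-reported medical parameters. CR attendance is not named.

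Methods for statistical analysis recognises that participation is not randomly assigned. Its answer is a score built on demographic and medical variables: "This propensity score will be used in the regression analysis of the effect of participation in CR on various outcomes". Dichotomous outcomes go to logistic regression.

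**The concern.** As described, a patient receives a participation status only by surviving to the point at which one-year mortality is counted. Exposure and outcome are then tied together by definition, and one-year mortality by participation carries no information about CR. Three-year mortality counted from surgery contains the same first year, so it can inherit the problem.

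A propensity score balances measured characteristics between participants and non-participants. It does not supply a status for patients who died before anyone asked, and it does not change the time at which status was defined.

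A survival benefit is the most consequential claim the study could make about CR. One plausible coding choice could produce it with no true effect.

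**Working it through.** **The plan's own figure.** The article gives no event count or power for mortality. Its only sample-size figure concerns participation by arm (7% against 14%, two-sided 0.05, 90% power). That figure reproduces: 401 per arm without and 430 with continuity correction, against the stated 430. It is not in question here.

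**Inputs.**
- p, the share of one-year survivors recorded as participants: 10.5%, the midpoint of the article's 7% and 14%.
- m1, one-year mortality: 3% or 5% (assumed).
- m3, three-year mortality: 8% or 12% (assumed).
- CR has no effect on death, so the true risk ratio is 1.00.

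**Rule A: first-year deaths are unclassified and drop out.**
- One year: every classified patient is alive, so mortality is 0% in both groups and no test is possible. This needs no assumption about rates.
- Three years: both groups have risk q = (m3 − m1)/(1 − m1), so the risk ratio is 1.00. But q is mortality in months 12 to 36. It ranges from 3.16% to 9.28%, against a three-year mortality of 8% to 12%. The share of three-year deaths left out is m1/m3, from 3/12 = 25% to 5/8 = 62.5%.

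**Rule B: first-year deaths are coded as non-participants.**
- One year: participants 0%; non-participants m1/[1 − p(1 − m1)].
- Three years: participants q; non-participants [m1 + (1 − p)(m3 − m1)]/[1 − p(1 − m1)].

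Example, m1 = 5% and m3 = 8%: q = 0.03/0.95 = 3.16%. Non-participants: (0.05 + 0.895 × 0.03)/(1 − 0.105 × 0.95) = 0.07685/0.90025 = 8.54%. Risk ratio 3.16/8.54 = 0.37.

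| m1 | m3 | One year, participants | One year, non-participants | Three years, participants | Three years, non-participants | Three-year risk ratio |
|---|---|---|---|---|---|---|
| 3% | 8% | 0% | 3.34% | 5.15% | 8.32% | 0.62 |
| 5% | 12% | 0% | 5.55% | 7.37% | 12.51% | 0.59 |
| 5% | 8% | 0% | 5.55% | 3.16% | 8.54% | 0.37 |
| 3% | 12% | 0% | 3.34% | 9.28% | 12.31% | 0.75 |

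Under rule B the spurious three-year ratio therefore runs from 0.37 to 0.75. Wider assumptions (first-year mortality 2-8%, then 2-3% a year, participation 10.5% or 25% of survivors) give 0.28 to 0.74.

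**The case against.** The strongest reply concerns three years. A reader might infer that the three-year comparison is biased whatever is done, or that hypothesis 2 would look confirmed even if CR did nothing. The article does not support either reading. It nowhere says that patients who died are coded as non-participants. If their status is simply missing, a regression on participation leaves them out, and what remains is in effect a 12-month landmark analysis with no differential immortal time. Nor can the one-year test confirm anything if no classified patient has died. This part of the reply stands, so the three-year claim is conditional.

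It can also be said that a condensed article leaves the mortality model, the time origin and the handling of early deaths to a full protocol or analysis plan. That is fair for the model. It does not rescue the one-year contrast, because the article itself fixes the hypothesis, the comparison groups, the time origin and the timing of ascertainment. A later plan would have to change one of these.

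Finally, mortality is one outcome among many under objective 3. The overall aim, the sample size and the comparison of arms on participation do not depend on it. That also stands and limits the reach of the point.

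**Conclusion.** The one-year survival hypothesis by CR participation is untestable as written: it has either no classifiable deaths or all of them in one group. This is structural and rests on no assumed rate, only on the article describing no source of attendance for patients who died.

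At three years the outcome depends on a rule the article does not state. Coding first-year deaths as non-participants gives a spurious risk ratio of 0.37-0.75 under no effect, at 10.5% participation and the assumed mortality of 3-5% and 8-12%. Excluding them gives an undistorted relative comparison, but of months 12 to 36 and not of three-year survival from surgery. The propensity score addresses confounding and resolves neither case.

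The flaw must be corrected for the survival part of hypothesis 2. It does not touch the main comparison of arms.

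**What to change.** 1. Remove one-year survival by CR participation from hypothesis 2 and from the participant versus non-participant outcome list, and align the Abstract. Report one-year mortality by study arm, as descriptive only, since the arms were recruited one after the other.
2. Keep a one-year contrast only if attendance with start dates is obtained for patients who died and CR is analysed as a time-dependent exposure. Attendance without dates is not enough, because a patient must still survive long enough to start.
3. Restate the long-term hypothesis as survival from one to three years after surgery among patients alive with known CR status at the one-year assessment. Analyse registry deaths from that landmark by propensity-adjusted regression, using a Cox model if the linkage supplies death dates; the article does not say whether it will.

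The landmark version changes the analysis wording and needs no new interviews. Its cost is that first-year deaths leave the participation analysis and precision falls. Under the assumptions above, with 1024 enrolled and all survivors classified, deaths among participants after the landmark would number about 3 (1024 × 0.95 × 0.105 × 3.16%) to 10 (1024 × 0.97 × 0.105 × 9.28%). The estimate will be imprecise and should be presented as such.
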